	**Study period**					
	**Enrolment**	**Allocation**	**Post-allocation**			
Timepoint	T0		*T1*	*T2*	*T3*	*T4*
**ENROLMENT**						
Informed consent	X					
Eligibility screen	X					
Psychiatrist /Psychotherapist Confirmation	X					
Allocation		X				
**INTERVENTIONS**						
Self-management intervention priovi® plus CAU						
CAU alone						
**ASSESSMENTS**						
Borderline personality disorder severity index (BPDSI)	X		X	X		X
Structured clinical interview for DSM-IV (SCID)	X		X	X		X
Adverse or serious adverse events	X		X	X		X
Borderline personality disorder checklist	X		X	X	X	X
9-item Patient Health Questionnaire (PHQ-9)	X		X	X	X	X
7-item anxiety scale (GAD-7)	X		X	X	X	X
Quality of life questionnaire (EQ-5D-3L)	X		X	X	X	X
Negative effects questionnaire (NEQ)			X	X	X	X
Self-reported uncontrolled internet use	X		X	X	X	X

*CAU, care as usual; T0, baseline; T1, 3 months; T2, 6 months; T3, 9 months; T4, 12 months*.

### Randomization

Participants are randomized equally (1:1) into two groups (intervention or control). Randomization is stratified by the presence of a diagnosis of BPD (probable vs. definite diagnosis of BPD). Block randomization with variable block sizes is used. The allocation schedule was created by an independent investigator with a computerized random number generator; the other investigators are blind to this schedule. The allocation sequence is concealed from participants and all trial staff. Only the unblinded trial staff is informed about the randomization outcome. The unblinded trial staff will not be included in data collection or evaluation and is instructed not to inform the raters about the randomization outcomes. Additionally, all participants are informed three times (at the end of the first interview, via the mail invitation for the second interview and at the beginning of the second interview) not to disclose their group assignment to their interviewer and to reserve questions about the usage of the intervention program exclusively for priovi support or the study team.

### Outcome measures

All outcome measures are used in their German version. The main outcome measure is the Borderline Personality Disorder Severity Index (BPDSI) (31, 32), a clinician-rated semi-structured interview that is based on the DSM-IV criteria for BPD. It assesses the frequency of BPD-manifestations during the past 3 months. It has excellent psychometric properties: Cronbach's α = 0.85 in patients with BPD and interrater reliability of 0.98. It also has excellent criterion-validity and change sensitivity. All raters will have a bachelor or master degree in psychology, have experience in psychological diagnostic assessments and will have participated in a rater training. Before they are permitted to rate trial participants, raters will have to demonstrate adequate interrater reliability on an audiotaped interview. For each rater, we will also assess the interrater reliability of their third interview.

Secondary study outcomes and safety parameters that will also be assessed during the diagnostic interview include the presence of a diagnosis of BPD on the structured clinical interview for DSM-IV (SCID) (33, 34) and the presence of adverse or serious adverse events. The assessment of adverse events follows recommendations established in pharmacological research (36). Using a semi-structured interview, participants are asked whether they have experienced any of the following events during the observation period (past 33 months for baseline and since last assessment for all other assessments): life-threatening events (e.g., self-injury, drug intoxication, accidents, etc.), medical occurrences that require hospitalization and suicide attempts.

The following secondary outcomes and safety parameters are then assessed using self-report: severity of BPD using the BPD-Checklist (37), depressive symptoms using the 9-item Patient Health Questionnaire (PHQ-9) (38), symptoms of anxiety using a 7-item anxiety scale (GAD-7) (39), quality of life (QoL) using the five-dimension three-level version of the questionnaire developed by the EuroQoL group (EQ-5D-3L) (40) and negative effects of the intervention using the Negative Effects Questionnaire (NEQ) (41). Participants are also asked about the parallel use of psychotherapy.

As a further safety parameter, we will employ a newly developed scale assessing self-reported uncontrolled internet use. It is based on the Compulsive Internet Use Scale (42) but comprises only two items that assess the frequency of using the internet longer than intended and avoiding work or family obligations due to internet use.

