### Participants

Patients will be included in the study if they have a total score of at least 15 on the BPD Severity Index (BPDSI) (31, 32) and a diagnosis of BPD according to DSM-5 (at least five definite criteria) (1) as assessed by the structured clinical interview for DSM-IV (SCID) (33, 34). A BPDSI score of below 15 has empirically been shown to be the cutoff for recovery of BPD (31). Patients can also be included, if they only meet the criteria for a probable BPD diagnosis (three definite and at least two probable of the DSM-5 criteria), but only if they have already received a diagnosis of BPD by their treating clinician. All patients also have to be at least 18 years of age; provide informed consent; have an adequate command of the German language; consult a psychiatrist/psychotherapist before randomization for confirmation of their diagnosis; be willing and able to participate in the planned diagnostic assessments. They will be excluded from participating in the trial if they meet diagnostic criteria for any of the following diagnoses on the MINI diagnostic interview (35): psychotic disorder (patients will not be excluded if they experience only transient, stress-related paranoid ideation that is consistent with a diagnosis of BPD); primary diagnosis of substance use disorder; schizotypal disorder.

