### Sample size

The sample size calculation is based on the expected difference between the intervention and the control group in the severity of BPD (measured with the BPDSI) at the 12 months assessment. Based on an estimated effect size of Cohen's *d* = 0.40, a power of 0.80 and an alpha level of 0.05, 100 participants are required in each condition resulting in a target sample size of *N* = 200. The effect size estimate was based on a recent meta-analysis (6), where the between-group effect for add-on designs (in which both groups received CAU and one group received an additional BPD therapy) was *g* = 0.40.

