### Statistical analysis

All continuous outcomes will be analyzed as a change from baseline with linear mixed models (LMM). These have the advantage of using all available data of each subject and they also offer the opportunity to choose an appropriate covariance structure reflecting the potential dependence due to repeated measurements (43). Adjustment for baseline measure will be chosen as this increases statistical power and accounts for regression to the mean (44). Missing values will be substituted using multiple imputations (with 50 imputations per missing value) to estimate missing scores by evaluating the relationships between observed and missing scores as well as baseline scores. For dichotomous outcomes, we will calculate logistic regression analyses that are adjusted for baseline values and time-to-event analyses (Kaplan–Meier survival analyses and Cox proportional hazards regression).

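### Adjusting the SCID-diagnosis outcome for its baseline value does nothing in the definite stratum; the baseline number of definite criteria would be an informative covariate

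*Protocol article*

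**What the plan says.** Under Participants, the main route into the trial is "a diagnosis of BPD according to DSM-5 (at least five definite criteria") on the SCID, with a BPDSI total of at least 15. A second route admits patients with a "probable BPD diagnosis (three definite and at least two probable of the DSM-5 criteria") who already carry a clinician's diagnosis. Randomization is stratified by definite versus probable diagnosis.

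Under Outcome measures, a secondary outcome is "the presence of a diagnosis of BPD on the structured clinical interview for DSM-IV (SCID"). Table 1 schedules the SCID at T0, T1 (3 months), T2 (6 months) and T4 (12 months). The number of criteria that must be met at follow-up is not restated.

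Under Statistical analysis, the rule is: "For dichotomous outcomes, we will calculate logistic regression analyses that are adjusted for baseline values". Kaplan–Meier and Cox analyses are planned as well. The same paragraph gives the reason for baseline adjustment when it introduces the mixed models: more power, and allowance for regression to the mean.

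**The concern.** The natural reading of a baseline value for a yes/no outcome is the same yes/no variable at T0. For this outcome, entry to the definite stratum fixed that variable at yes. The planned adjustment then has nothing to work with, although selection at a threshold is where regression to the mean is to be expected. A patient admitted with five criteria needs one criterion to be rated lower to lose the diagnosis; a patient with nine needs five. That difference predicts the outcome strongly, and the T0 interview records it, but the covariate discards it.

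At stake is the precision of one secondary comparison. A real reduction in BPD criteria would more often appear as no clear effect on diagnosis than it need do.

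**Working it through.** **1. The plan's own figure.** The Sample size section gives "Based on an estimated effect size of Cohen's *d* = 0.40", "a power of 0.80 and an alpha level of 0.05", and concludes that "100 participants are required in each condition resulting in a target sample size of" 200. Two-sided, n per arm = 2(1.960 + 0.842)²/0.40² = 98.1, so 99; the t-test version gives 99.08, rounded up to 100. Power at 100 per arm is Φ(0.40·√50 − 1.960) = Φ(0.868) = 0.81. The figure reproduces. It concerns the continuous BPDSI, not the SCID outcome, and is used below only for the 100 per arm.

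**2. What the baseline covariate can carry.** There are two readings of who has the diagnosis at T0.

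- Present means at least five definite criteria: the covariate is 1 for every definite patient and 0 for every probable patient, so it equals the stratification factor.
- Probable also counts as present: the covariate is 1 for every patient in the trial.

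On either reading it is constant within the definite stratum and holds nothing beyond the stratum indicator. This step needs no assumed number.

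**3. How much the baseline count matters near the cut.** Assume a follow-up cut of five, no true change, and an independent misrating probability q for each of nine criteria. For a patient truly meeting k criteria, let A be those still rated met and B those wrongly rated met. The chance of a rating below five is

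P(A + B < 5), with A ~ Bin(k, 1 − q) and B ~ Bin(9 − k, q).

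For k = 5 and q = 0.05: P(A=4)·P(B=0) + P(A=3)·P(B≤1) + P(A≤2) ≈ 0.2036·0.8145 + 0.0214·0.986 + 0.0012 ≈ 0.188.

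| True criteria | q = 0.05 | q = 0.10 |
|---|---|---|
| 5 | 0.188 | 0.293 |
| 6 | 0.028 | 0.087 |
| 7 | 0.003 | 0.021 |
| 8 | 0.000 | 0.005 |

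A second model uses a count of 0–9 with SD 2 and mean 5.5 or 6.5 before selection, entry at an observed count of at least 5, retest reliability 0.7–0.9 and no true change. Patients observed at exactly five lose the diagnosis at T4 through noise in 23–32% of cases, against at most 2% of those at eight or more. Over the whole definite group the figure is 5–16%.

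**4. Power at T4.** To the second model add a natural decline of 1.0 criterion (SD 1.5) in both arms and a treatment effect of 0.8 criteria, with 100 per arm, all from the definite stratum. Across the two means and reliabilities 0.7–0.9:

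| Analysis | Power |
|---|---|
| Diagnosis present or absent, unadjusted (equivalent to adjusting for baseline presence) | about 47–56% |
| Diagnosis present or absent, logistic model with baseline count | about 52–65% |
| Count as continuous outcome, adjusted for baseline count | about 75–88% |

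The covariate alone adds about 5 points at the lower ends (52 − 47) and 9 at the upper ends (65 − 56). Repeated runs differ by a few points.

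**5. Cross-check by another route.** If a normal outcome with d = 0.40 is cut to yes/no at an assumed control rate of 20%, the treated rate is Φ(−0.842 + 0.40) = 0.329 and power with 100 per arm is 0.55. Control rates of 10% to 40% give 0.43 to 0.61, against 0.81 for the continuous comparison.

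**The case against.** Presence of a diagnosis is a standard, readable endpoint, and nothing in the article contradicts its use. The follow-up cut of five definite criteria is an inference, and baseline values could be meant to include the criterion count. The full analysis plan, not shown, may settle both. These points stand, and they are why this is a request to specify the covariate rather than a claim of error.

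A reader might infer more: that rating noise makes the outcome unreliable, that the rate of lost diagnoses is overstated by 5–16 points, or that the diagnosis should become descriptive or need confirmation at two visits. The documents do not support this.

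- Raters are blinded and patients randomised, so the noise falls equally on both arms and creates no false difference.
- The 5–16% assumes that no patient truly changes. With true decline, some patients who have fallen below the cut are rated above it. In the decline model, the control rate moves only from 38% to 34% (mean 5.5), or from 28% to 26% (mean 6.5), as reliability rises from 0.7 to 0.9.
- The gap between the first and third rows of the power table mixes two things: using the count, and adjusting for baseline. Without adjustment on either side, a separate run gave 46–58% for the diagnosis and 65–75% for the count.
- The article gives no SCID reliability (its 0.98 is for the BPDSI) and no distribution of baseline criteria.

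BPD severity is also already analysed continuously through the BPDSI and the BPD-Checklist. A null result on diagnosis would be read beside those.

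**Conclusion.** The point holds in a narrow form. In the definite stratum, adjustment for baseline presence of the diagnosis is adjustment for a constant. It delivers neither of the benefits that the article cites for baseline adjustment. This follows from the entry rule and needs no assumption about noise.

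The size does rest on assumptions: a follow-up cut of five definite criteria, SD 2, mean 5.5–6.5, reliability 0.7–0.9, a decline of 1.0, an effect of 0.8 criteria, and 100 per arm with no dropout. Under these, the better covariate is worth roughly 5 to 9 points of power, and the count as a supporting outcome considerably more. The planned test remains valid, and the primary analysis and sample size are untouched. Minor severity, one secondary outcome.

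**What to change.** In the Statistical analysis section, state that the logistic model for the SCID diagnosis, and the Cox model if it is used for this outcome, adjusts for the number of definite criteria at the T0 SCID together with the definite/probable stratum. Add the number of definite criteria (0–9) at T1, T2 and T4 as a supporting continuous outcome in the baseline-adjusted mixed model already planned. Keep presence of the diagnosis as the listed secondary outcome, and state the follow-up cut in one sentence.

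No new data or visits are needed, because the entry rule already requires the criteria to be counted at T0 and the SCID is scheduled again at T1, T2 and T4. The cost is one additional supporting analysis and an odds ratio that is conditional on the baseline count. As the trial is already recruiting, the change should be dated before unblinding and, if handled as an amendment, sent to the ethics committee and posted as the Ethics statement provides.

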### Procedure and assessments

After providing online informed consent, all prospective participants will be assessed via an online questionnaire and a telephone interview to establish if the inclusion criteria have been met. The assessment by online questionnaire and telephone interview will also be used to establish the baseline (T0). At the end of the telephone interview an individual crisis plan is discussed with all participants, i.e., whether they have contact information at hand of people they could contact in case of an acute crisis, e.g., acute suicidal ideation or impeding severe self-injury. Crisis contacts include both professionals (psychiatrists/psychotherapists) and friends. All participants will also be made aware of the nationwide emergency number−112.

Following the telephone interview, eligible participants will have to ask a psychiatrist or psychotherapist to confirm in writing (using a form supplied by the study staff) that they are suitable for participating in an RCT of a self-management intervention for BPD. After the receipt of this confirmation by a psychiatrist/psychotherapist, participants will then be randomized. They are contacted again after 3 months (T1), 6 months (T2), 9 months (T3), and 12 months (T4). All assessments include an online questionnaire and a telephone interview except for the T3 assessment that only comprises an online assessment. All assessments and the respective measures to be used can be found in Table 1.

**Table 1 T1:** Schematic diagram of study timeline.

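### The adverse-event recall windows are badly fixed: an unexplained 33 months at baseline, a T1 window that opens before randomization, and an ambiguous window at T4

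*Protocol article*

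**What the plan says.** All references are to the protocol article.

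- *Outcome measures* describes how adverse events are collected: "Using a semi-structured interview, participants are asked whether they have experienced any of the following events during the observation period". The period is then defined in a parenthesis: "past 33 months for baseline and since last assessment for all other assessments". The events are life-threatening events, hospitalizations and suicide attempts.
- The same section gives the look-back of the primary outcome, the BPDSI: "It assesses the frequency of BPD-manifestations during the past 3 months".
- *Table 1* gives the schedule: "T0, baseline; T1, 3 months; T2, 6 months; T3, 9 months; T4, 12 months". Its row "Adverse or serious adverse events" is marked at T0, T1, T2 and T4 and is blank at T3.
- *Procedure and assessments* says that every assessment combines an online questionnaire with a telephone interview, "except for the T3 assessment that only comprises an online assessment". The T0 interview comes first, then the participant obtains written confirmation from a clinician. "After the receipt of this confirmation by a psychiatrist/psychotherapist, participants will then be randomized".
- *Statistical analysis* plans, for dichotomous outcomes, "logistic regression analyses that are adjusted for baseline values and time-to-event analyses".
- *Data management* compares serious adverse event frequencies between the groups during internal audits and ties early termination to that comparison.

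**The concern.** The recall window decides which events are counted, and here it is loose at three of the four adverse-event interviews.

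At baseline, 33 months stands without a reason next to intervals of 3 and 6 months everywhere else. At T1, the previous assessment is T0, which happens before allocation. At T4, the previous assessment is either T3, where nobody asks about adverse events, or T2, where somebody does.

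Safety is one of the trial's two stated aims. The article presents interview-based assessment of serious adverse events as a distinguishing strength, and the early-termination rule uses the resulting counts without an independent monitoring committee. If interviewers or participants apply the windows differently, or some events precede randomization, the between-group comparison and any survival analysis timed from randomization rest on poorly defined counts.

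**Working it through.** The article gives no derivation for the 33 months, so there is no calculation of its own to reproduce. The sample size does not enter this point. The check is interval arithmetic on the schedule.

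**Inputs.** Adverse-event interviews at months 0, 3, 6 and 12, and all assessments at months 0, 3, 6, 9 and 12 (*Table 1*). BPDSI look-back 3 months and baseline adverse-event look-back 33 months (*Outcome measures*). Randomization after T0 (*Procedure and assessments*).

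**Step 1: baseline.** Successive adverse-event interviews are 3 − 0 = 3, 6 − 3 = 3 and 12 − 6 = 6 months apart. The BPDSI window is 3 months. None of these is near 33, and 33 / 3 = 11.

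To see what hangs on the figure, assume a constant probability p of at least one event per 3 months. The article gives no rate, so p is varied. The proportion with at least one event in m months is 1 − (1 − p)^(m/3).

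| Assumed p (3 months) | 33 months, exponent 11 | 12 months, exponent 4 | 9 months, exponent 3 |
|---|---|---|---|
| 5% | 43% | 19% | 14% |
| 10% | 69% | 34% | 27% |
| 20% | 91% | 59% | 49% |

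For example, 1 − 0.95^11 = 0.43. A 33-month and a 3-month baseline question therefore produce very different covariates: 43% against 5% positive in the first row.

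**Step 2: T1.** Let g be the time in months from the T0 interview to randomization. It is positive, because the clinician's confirmation comes in between, but its length is not stated. Assume that T1 falls 3 months after randomization and that the event rate is constant. The T1 window then has length g + 3, of which g is before allocation. If the true rate ratio after randomization is R, the ratio expected from the T1 counts is (g + 3R) / (g + 3). For any g > 0 this lies between 1 and R. If T1 is instead timed from T0, the expression is (g + (3 − g)R) / 3, again between 1 and R. Both show dilution, whichever meaning the phrase has at T4. The amount cannot be computed without g.

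**Step 3: T4.** The phrase has two readings.

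| Reading of the previous assessment | Windows (months) | Covered |
|---|---|---|
| Any assessment, so T4 looks back to T3 | 0-3, 3-6, 9-12 | 3 + 3 + 3 = 9 of 12 |
| Last adverse-event interview, so T4 looks back to T2 | 0-3, 3-6, 6-12 | 3 + 3 + 6 = 12 of 12 |

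On the first reading 3/12 = 25% of follow-up lies in no window. On the second, none does. The last two columns of the Step 1 table show the effect on the proportion with any event: for instance 14% instead of 19% at p = 5%.

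The Negative Effects Questionnaire given at T3 does not close the gap on the first reading. It is a self-report of negative effects of the intervention, not the adverse-event interview.

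**The case against.** A reader might infer that months 6-9 are never asked about and that a quarter of follow-up is unobserved. The article does not support that as a fact. The recall rule is a parenthesis inside the description of the adverse-event interview, and the other assessments it mentions can only be those where that interview is held. Read that way, T4 looks back to T2 and all 12 months are covered. This reading is at least as natural as the literal one. What remains is that the article elsewhere calls T3 an assessment, so the T4 window is open to two interpretations.

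A reader might also infer that the safety comparison or the early-termination rule is biased toward one arm. That does not follow. Omitted months would be omitted in both arms, and events before randomization are independent of allocation. The first costs events and power; the second dilutes the contrast. It is also fair that the gap before randomization is unquantified, and that an interview guide not shown here may record event dates.

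On the baseline window, a covariate need not share the outcome's time scale, and adjusting for a longer history does not bias a randomized comparison. This stands, so the harm from 33 months is limited. It also cannot be proved from the article that 3 months was meant. The figure is nonetheless an operational instruction that is unexplained and out of line with everything around it.

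**Conclusion.** The point holds as a defect of definition, not as a demonstrated loss of data.

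- The 33-month baseline window is probably a slip. It is 11 times the BPDSI look-back and matches no interval in the schedule. Its practical consequence is a differently scaled baseline covariate; the 43%, 69% and 91% figures depend on assumed 3-month event probabilities of 5%, 10% and 20%.
- The T1 window includes time before randomization under either reading of the phrase. It dilutes the between-group safety contrast and puts events into the counts that have no valid place in analyses timed from randomization. The size is unknown because the gap is not stated.
- The T4 window is ambiguous. Between 0 and 3 of the 12 follow-up months fall outside every window, depending on the reading; a 25% loss of events needs both the literal reading and a constant event rate.

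Followed literally, the rule gives worse safety counts than the schedule allows. The correction is cheap enough to make whichever reading was intended.

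**What to change.** Reword the recall rule in the protocol and the interview guide, reconciling it with *Table 1*:

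1. Baseline: confirm against the interview guide which window is in use, then correct the 33 months or state why it was chosen.
2. T1: ask about events since randomization.
3. T2 and T4: ask about events since the last completed adverse-event interview. At T4 this is normally T2; the word completed also covers a missed interview.
4. Record the date of each event, so that anything between T0 and randomization can be separated out and time-to-event analyses have a usable origin.

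No visit, staff or online item needs to be added. The costs are a wording change, a date field and, as the one small downside, a 6-month recall at T4.
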